### Outcome

This study will evaluate the Oswestry Disability Index (ODI), Numerical Rating Scale (NRS), Pain Catastrophizing Scale (PCS), Fear Avoidance Beliefs Questionnaire (FABQ), EQ-5D-5L, the Flexibility Test, and the muscle strength test in the fourth week of the experiment. Furthermore, the results of the ODI, NRS, PCS, FABQ, and EQ-5D-5L will be followed up at the 8th and 16th weeks. The schedule of evaluations is outlined in Table 1 (Multimedia Appendix 2).

**Table 1 table1:** Schedule of enrollment, intervention, and outcome measures.

Enrollment	Screening and allocation	Treatment period		Follow-up period	
	Week 0	Week 1-3	Week 4	Week 8	Week 16
Inclusion or exclusion criteria	✓	—^a^	—	—	—
Informed consent form	✓	—	—	—	—
Medical history	✓	—	—	—	—
Physical examination	✓	—	—	—	—
Eligibility for study	✓	—	—	—	—
Baseline characteristics	✓	—	—	—	—
C-spine x-ray	✓	—	—	—	—
Allocation	✓	—	—	—	—
Intervention	—	—	—	—	—
Yijinjing^b^	—	—	—	—	—
SSE^b,c^	—	—	—	—	—
Outcomes	—	—	—	—	—
ODI^d^	✓	—	✓	✓	✓
NRS^e^	✓	—	✓	✓	✓
PCS^f^	✓	—	✓	✓	✓
FABQ^g^	✓	—	✓	✓	✓
EQ-5D-5L	✓	—	✓	✓	✓
Flexibility test	✓	—	✓	—	—
Muscle strength test	✓	—	✓	—	—

^a^Not applicable.

^b^Two times a week from weeks 1-4.

^c^SSE: self-stretching exercises.

^d^ODI: Oswestry Disability Index.

^e^NRS: Numeric Rating Scale.

^f^PCS: Pain Catastrophizing Scale.

^g^FABQ: Fear Avoidance Beliefs Questionnaire.

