### Statistical Analysis

In this study, the principle of intentionality analysis will be used to analyze the data. The safety analysis set will be used to analyze the safety of this study. A statistician who is unaware of the group assignments will use SPSS statistical software (version 26.0; IBM Corp) to analyze the data. All effects will be estimated using 95% CIs, and all the statistical tests will be 2-sided. A *P* value less than .05 indicated statistical significance.

Continuous variables are presented as the mean (SD) if they follow a normal distribution; otherwise, they are presented as medians and quartiles. Categorical variables are presented as percentages. Primary outcomes will be assessed using analysis of covariance adjusted for baseline. For other secondary outcomes, *t*-tests or Wilcoxon rank-sum tests will be used.

Repeated outcomes over time will be compared using linear mixed-effects models with the following fixed effects: (1) time points (categorical), (2) intervention group, (3) time-by-group interaction, and (4) baseline measurement as a covariate. Random intercepts for participant ID will be included to account for within-subject correlations. Additional adjustments will be made for prespecified covariates, including age, gender, and study site (if multicenter). Bonferroni correction was used for multiple comparisons across time points.

Missing data will be replaced according to the principle of carry-over of last observations. Missing values for dropout cases will be imputed using either the last observation carried forward method if the dropout rate is below 5% or the multiple imputation method for a dropout rate of 5% or higher. If the attrition rate exceeds 10%, we use per-protocol analysis to ensure the reliability of this study.

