## Discussion

### Principal Findings

This study aims to provide critical evidence to support the therapeutic efficacy of Yijinjing intervention for CLBP. There is a lack of high-quality clinical trials on the effects of Yijinjing in CLBP, although we found some clinical evidence of this approach in patients, we hypothesize that a 12-week Yijinjing regimen will yield clinically meaningful improvements in functional disability, lumbar muscle strength, and pain intensity, with durable therapeutic effects persisting through a 3-month follow-up period. Crucially, concurrent improvements in emotional distress measures and lumbar flexibility would suggest that Yijinjing confers multidimensional benefits extending beyond biomechanical adaptations—a finding that could redefine its role as a holistic intervention addressing both somatic and psychosocial dimensions of CLBP. While existing literature substantiates the moderate efficacy of exercise therapies in CLBP management [40], Yijinjing’s distinctive focus on graded neuromuscular control and dynamic muscular equilibrium [41] differentiates it from conventional strength training paradigms, potentially offering unique mechanistic advantages.

This study’s strengths include multidimensional outcome assessment (functional, physiological, and psychological domains) and longitudinal follow-up. However, 3 limitations warrant acknowledgment: first, inherent challenges in participant blinding for behavioral interventions may introduce expectation bias in self-reported outcomes, though objective biomechanical measurements partially mitigate this concern. Second, the single-center recruitment strategy may constrain population generalizability. Third, while the pragmatic 30-minute intervention protocol enhances clinical translatability, it precludes exploration of dose-response relationships relative to extended regimens.

In conclusion, this trial will systematically evaluate Yijinjing’s efficacy and safety profile in CLBP management. Its findings may inform clinical guidelines for integrating traditional mind-body exercises into contemporary pain rehabilitation frameworks. Nevertheless, given the constrained intervention duration inherent to this design, subsequent investigations should prioritize extended treatment phases and prolonged follow-up windows to elucidate long-term outcomes and potential decay patterns of therapeutic benefits.

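### The repeated-outcome mixed model names only random intercepts for within-subject correlation; if correlation decays with time, individual between-visit contrasts are miscalibrated in both directions (minor)

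*Protocol article*

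**What the plan says.** The Statistical Analysis section sets out the longitudinal model: "Repeated outcomes over time will be compared using linear mixed-effects models with the following fixed effects". These are categorical time, group, their interaction, and "baseline measurement as a covariate". Age and gender are added as covariates. For the correlation between a participant's visits it says: "Random intercepts for participant ID will be included to account for within-subject correlations". It names no residual covariance structure, robust variance or degrees-of-freedom method.

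Because baseline is a covariate, the repeated response has three levels. Under Outcome, assessment takes place in week 4, and ODI, NRS, PCS, FABQ and EQ-5D-5L "will be followed up at the 8th and 16th weeks". Flexibility and muscle strength stop at week 4, so the model concerns the five questionnaires.

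On error control the section states "A *P* value less than .05 indicated statistical significance", with two-sided tests and 95% CIs for all effects, and "Bonferroni correction was used for multiple comparisons across time points". The primary analysis is listed separately: "Primary outcomes will be assessed using analysis of covariance adjusted for baseline". The Discussion (Principal Findings) expects "durable therapeutic effects persisting through a 3-month follow-up period".

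**The concern.** A random intercept with independent residuals is a compound-symmetry model. Week 4 is taken to correlate with week 16 as strongly as with week 8, and the spread is taken to be the same at the end of treatment as 12 weeks later. Neither is a comfortable assumption for visits 4 and 8 weeks apart, one closing the treatment period and two falling after it.

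With complete data the estimates themselves are not biased by this. The standard errors are at stake. The model uses one average variance for every between-visit contrast, so it understates the uncertainty of contrasts between distant visits and overstates it for close ones. It likewise uses one average variance for the group difference at each visit. The Bonferroni step changes the threshold but not the standard error, and the promised 95% CIs carry the same fault.

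**Working it through.** **Inputs.** From the documents: three outcome visits (weeks 4, 8, 16), 53 per arm, two-sided 5%, Bonferroni across time points. The plan states no variance, correlation or error rate for this model, so there is no figure of its own to reproduce. Assumed: all correlations and variance patterns below, complete data, and three contrasts for Bonferroni (0.05/3 = 0.0167).

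**Between-visit contrasts, equal variances.** In units of the common variance, the variance factor for visits j and k is 2(1 − ρ_jk). The random-intercept model uses the mean of the three factors for all of them. With R = true/model variance, the rejection rate under the null is 2[1 − Φ(z/√R)], with z = 1.96.

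Strong decay, correlations 0.8 (weeks 4-8), 0.65 (8-16) and 0.5 (4-16):

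- True factors: 2(0.2) = 0.4, 2(0.35) = 0.7, 2(0.5) = 1.0.
- Model factor: (0.4 + 0.7 + 1.0)/3 = 0.7.

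| Contrast | R | Rejection at nominal 5% |
|---|---|---|
| Week 8 − week 4 | 0.4/0.7 = 0.571 | 1.0% |
| Week 16 − week 8 | 0.7/0.7 = 1.00 | 5.0% |
| Week 16 − week 4 | 1.0/0.7 = 1.43 | 10.1% |

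For week 16 − week 4 the model SE is √0.7 = 0.837 of the true SE, so a nominal 95% CI covers about 90%. For week 8 − week 4 it covers about 99%.

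Milder decay, week 16 − week 4:

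- 0.7, 0.7, 0.6: factors 0.6, 0.6, 0.8; mean 0.667; R = 1.20; rejection 7.4%.
- 0.7, 0.6, 0.5: factors 0.6, 0.8, 1.0; mean 0.8; R = 1.25; rejection 8.0%.

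A rate of 10% needs R = 1.42.

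**After Bonferroni.** For the strong-decay week 16 − week 4 contrast, the critical value is z = 2.394; 2.394 × 0.837 = 2.00, giving 4.5% against 1.67%.

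**Group difference at a single visit.** The model uses the average variance over visits. With equal variances R = 1, and the test is near nominal whatever the correlations. If the variances run 0.7 : 1 : 1.3 (mean 1):

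- Week 16: R = 1.3, rejection 8.6% (simulated 8.5%), and 3.6% at the Bonferroni level.
- Week 4: R = 0.7, rejection 1.9% (simulated 1.8%).

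With 0.85 : 1 : 1.15, week 16 gives 6.8%. If the variance falls over time, the direction reverses and week 16 becomes conservative.

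**Simulation check.** The random-intercept analysis with a baseline covariate was simulated under the null, with 20,000 replicates per scenario at 53 per arm:

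| Quantity | Rejection rate over scenarios |
|---|---|
| Week 16 − week 4, compound symmetry true | 5.1% |
| Week 16 − week 4, mild decay (the two patterns above) | 7.3-7.9% |
| Week 16 − week 4, serial decay, 4-week correlation 0.7 to 0.9 | 9.0-10.1% |
| Week 16 − week 4, variance also growing strongly | 11.1-11.4% |
| Week 8 − week 4, not compound symmetric | 0.3-3.9% |
| Week 16 − week 8 | 3.6-6.4% |
| Overall interaction F test | 5.1-6.6% |
| Week-16 group difference, equal variances | about 5% |
| Week-16 group difference, week-16 variance larger | 7.5-13.0% |
| Familywise, Bonferroni, between-visit contrasts | 4.5-5.8% |
| Familywise, Bonferroni, group difference at each visit | 3.4-6.9% |

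Two scenarios repeated at 42 per arm gave 9.3% and 7.9% for week 16 − week 4, so fewer participants do not change the picture.

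**The case against.** The strongest reply is that the article does not say the random intercept is the only covariance term. A residual structure can be added to the same model, and an article commonly leaves that detail to the analysis plan. This stands as far as it goes: a reader might infer that the plan rules out anything else, and the text does not support that. But the section does more than stay silent. It names random intercepts as the means of handling within-subject correlation, and an analyst who follows that sentence fits compound symmetry.

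A reader might also infer that the model doubles the false-positive rate of the tests behind the durability claim. The documents do not support that either. No section names a deciding contrast. A week 16 minus week 4 interaction contrast tests whether the effect changed, so a false rejection there signals growth or waning rather than persistence. Lasting benefit is naturally read from the group difference at week 16, which is near nominal with equal variances. Nor does the inflation apply to the time-by-group contrasts generally: one of the three is inflated, to about 10% only under strong decay, and one is conservative.

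It is also fair to say that Bonferroni keeps the familywise error near nominal. That holds partly because a conservative contrast offsets a liberal one. It does not correct the individual test or its CI.

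Finally, every correlation and variance used is assumed, and the calculations take complete data although the sample-size section expects 20% dropout.

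**Conclusion.** The point holds as a minor one. The only correlation device the plan names implies equal variance and equal correlation across three unequally spaced visits that span the end of treatment. If correlation decays with time, the SEs and 95% CIs of individual between-visit time-by-group contrasts are wrong in both directions: too small for week 16 minus week 4, too large for week 8 minus week 4. The week-16 group difference goes wrong only if the variance changes across visits: too liberal if the week-16 variance is larger, too conservative if it is smaller. The overall interaction test and the familywise error move little, and the baseline-adjusted ANCOVA for the primary outcome does not depend on this choice. The sizes rest wholly on assumed covariance patterns. If compound symmetry is true, nothing is wrong.

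**What to change.** Keep the stated fixed effects. In SPSS, replace the random intercept by a REPEATED visit effect with unstructured covariance and Satterthwaite degrees of freedom, and name heterogeneous Toeplitz as the fallback if the model does not converge. If a separate analysis plan already specifies this, it is enough to align the article's sentence with it.

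Three visits need 6 covariance parameters (3 variances and 3 covariances) against 2 for the random-intercept model, so 4 more, which 106 participants support. Compound symmetry is a special case, so little is lost if it is true. The cost is a wording change, a small change of code and a slight risk of non-convergence. The article reports that analysis had not begun, so at that stage the change could be made without sight of results.

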### Sample Size Calculation

The calculations are based on hypothetical changes in the ODI at week 6. We use the results of a randomized controlled trial to formulate the intended effect. We hypothesize a 3.57-point improvement on the ODI scale in the Yijinjing group compared to the control group [20]. The sample size for each group provided 90% power, and these differences were detected using PASS software (version 15.0.5; NCSS, LLC) at a 2-sided significance level of .05. Considering an expected dropout rate of 20%, a total of 106 patients are required for this study.

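### Holm's step-down procedure would be a cheap gain over plain Bonferroni for the repeated outcomes; the planned correction is valid but less powerful at the same family-wise error

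*Protocol article*

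**What the plan says.** The Statistical Analysis section compares repeated outcomes with a linear mixed model containing time, group, their interaction and the baseline value. It closes that paragraph with "Bonferroni correction was used for multiple comparisons across time points". It does not say which comparisons form the family or how many there are.

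The Outcome section and Table 1 place a first post-baseline assessment at week 4, and the ODI, NRS, PCS, FABQ and EQ-5D-5L "will be followed up at the 8th and 16th weeks". That makes three post-baseline visits for these five outcomes. Flexibility and muscle strength are measured after baseline at week 4 only.

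Three other statements bear on the point:
- **Primary outcome.** A separate paragraph says "Primary outcomes will be assessed using analysis of covariance adjusted for baseline".
- **Intervals.** "All effects will be estimated using 95% CIs, and all the statistical tests will be 2-sided".
- **Sample size.** "The sample size for each group provided 90% power", "at a 2-sided significance level of .05", which is a single comparison with no allowance for several visits.

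The Principal Findings section expects a benefit "with durable therapeutic effects persisting through a 3-month follow-up period".

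**The concern.** Single-step Bonferroni holds every comparison in the family to the same strict threshold. Holm orders the P values and relaxes the threshold after each rejection. With three comparisons the thresholds are .0167, .025 and .05, against .0167 throughout for Bonferroni. Holm needs no extra assumption about the correlation between visits.

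The difference matters most when true effects exist at several visits, which is the pattern this trial hypothesises. With a lasting benefit of equal size, the stricter rule more often gives a split picture, significant at some visits and not at others. What is at stake is how clearly durability can be shown for the repeated outcomes. Error control is not at stake.

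**Working it through.** **Inputs from the protocol.** Two-sided level .05; power 90%; difference 3.57 ODI points; dropout 20%; total 106, 53 per arm; visits at weeks 4, 8 and 16.

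**Inputs assumed.** A family of three group contrasts per outcome, the planned standardised effect at each visit unless stated otherwise, and equal correlation between visit statistics of 0.4 to 0.8. The protocol gives none of these.

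**1. The plan's own figure.** The article gives no ODI standard deviation, so 106 can only be back-solved.
- n per arm = 2 × SD² × (1.960 + 1.2816)² / 3.57².
- With SD = 5.0: 2 × 25 × 10.507 / 12.745 = 41.2, so 42 per arm.
- Allowing for dropout: 42 / 0.8 = 52.5, so 53 per arm and 106 in total.

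The stated size fits an SD of about 5.0. The comparison below does not need the SD, because 90% power at two-sided .05 fixes the expected test statistic at z = 1.960 + 1.2816 = 3.2415.

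**2. Bonferroni, per visit.** Level .05 / 3 = .0167, critical value 2.394. Power = 1 − Φ(2.394 − 3.2415) = 80.2%.

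**3. Holm, planned effect at all three visits.** Simulation with 1,000,000 draws of three correlated normal statistics:

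| Correlation | Per visit: Bonferroni | Per visit: Holm | All three: Bonferroni | All three: Holm | Some but not all: Bonferroni | Some but not all: Holm |
|---|---|---|---|---|---|---|
| 0.4 | 80% | 87% | 59% | 76% | 37% | 21% |
| 0.6 | 80% | 86% | 64% | 78% | 30% | 16% |
| 0.8 | 80% | 85% | 69% | 81% | 21% | 9% |

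**4. Effect fading to 60% at week 16 (correlation 0.6).** The week-16 statistic is centred at 0.6 × 3.2415 = 1.945.
- Bonferroni power = 1 − Φ(2.394 − 1.945) = 33%.
- Holm gives 45% if week 8 keeps 80% of the effect, and 48% if week 8 keeps all of it.

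**5. Where nothing is gained.**
- At least one visit significant: identical under both methods, because Holm's first step is the Bonferroni test. With the effect at all visits this is 87-99% over correlations 0.9 to 0.
- Effect at week 4 only: 80% at week 4 under either method.

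**6. Error control.** With no effect at any visit, family-wise error at correlation 0.6 is 4.2% under both. Over correlations 0 to 0.9 it runs from 4.9% down to 3.0%.

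**The case against.** The strongest case against is that Bonferroni is a valid, prespecified method, and a more powerful alternative does not make it wrong. That stands, and it is why this is offered as an improvement only.

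Bonferroni also has a real advantage. It gives simultaneous intervals that agree with its tests (98.3% per visit for three visits), and Holm has no simple equivalent. A reader might infer that the present choice buys nothing, and that is not so. The advantage is small here because the plan promises 95% intervals and does not mention simultaneous ones.

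The figures also describe a favourable case:
- The effect size was set for the ODI at one time point, week 6, which is not a scheduled visit. No effect size is given for the NRS, PCS, FABQ or EQ-5D-5L.
- Significance at all three visits is nowhere made a criterion of success.
- If the family is comparisons between visits, Holm still never rejects less, but these figures do not apply. With a constant group effect there would be no true between-visit difference in that effect to find.

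Two stronger readings are tempting. One is that visit effects will be missed because of the correction. They are only more likely to be missed, and Holm itself leaves a split result in 9-21% of trials in the table. The other is that the primary conclusion is affected. The protocol does not support this, because the Bonferroni sentence belongs to the mixed-model paragraph and the primary analysis of covariance stands apart.

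**Conclusion.** The point holds as a cheap improvement. At the same family-wise error, Holm adds about 5 to 7 percentage points of power per visit and about 12 to 17 points for showing the effect at all three visits. If the effect fades to 60%, it adds about 12 to 15 points at week 16. These sizes rest on an inferred family of three, the planned ODI effect carried to the scheduled visits, and assumed correlations. That Holm never rejects less than Bonferroni rests on none of these. The gain is nil for detecting any visit effect and about nil if only one visit has an effect.

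**What to change.** Replace the Bonferroni sentence in the Statistical Analysis section with: 'Within each repeated outcome, the group comparisons at weeks 4, 8 and 16 from the mixed model are tested with Holm's step-down procedure at a two-sided family-wise level of .05.' This also states the family.

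Report the planned 95% intervals. If simultaneous intervals are wanted, show Bonferroni-level ones, labelled conservative, with a note that such an interval may include zero where the Holm test is significant.

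The cost is one sentence and no new software, since three P values are ordered by hand. Timing is the real constraint. The article reports 106 participants recruited by August 2024, so week-16 follow-up would end around December 2024. It also says that analysis had not begun. Holm can only add rejections, so the change must be made before unblinding and documented as a change. If the data are already unblinded, Bonferroni should stay.

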**Methods:**

This is a 2-arm, parallel-design, assessor-blinded, and analyst-blinded randomized controlled trial. The 106 participants with CLBP who were recruited will first receive basic traditional Chinese manual therapy to help relieve their physical discomfort. Second, they will be randomly divided into a Yijinjing group (n=53) and a control group with functional exercises (n=53) at a ratio of 1:1. The interventions for both groups will be carried out twice a week for 4 weeks. Patients in both groups will be followed up at 1 and 3 months after the intervention. The primary outcome is disability (measured by the Oswestry Disability Index). The secondary outcomes included pain intensity (assessed by the Numerical Rating Scale), data from isokinetic dynamometry, flexibility (assessed by the fingertip-to-floor test), mood (evaluated by the Pain Catastrophizing Scale and Fear Avoidance Beliefs Questionnaire), and quality of life (measured by the EQ-5D-5L). All adverse effects will be assessed using the Treatment Emerging Symptoms Scale, and data will be analyzed using an intention-to-treat analysis.

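### Three unranked missing-data rules give three different answers at the trial's own planned 20% dropout, and one of them departs from intention-to-treat

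*Protocol article*

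**What the plan says.** All three rules stand in the last paragraph of the Statistical Analysis section of the protocol article.

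- **Rule 1, no condition:** "Missing data will be replaced according to the principle of carry-over of last observations".
- **Rule 2, by dropout rate:** dropout cases get LOCF if dropout is below 5%, and otherwise "the multiple imputation method for a dropout rate of 5% or higher".
- **Rule 3, by attrition:** "If the attrition rate exceeds 10%, we use per-protocol analysis to ensure the reliability of this study".

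The same section opens with "In this study, the principle of intentionality analysis will be used to analyze the data", which the Abstract makes plain: "data will be analyzed using an intention-to-treat analysis". The Sample Size Calculation section assumes 20% dropout and a total of 106. The primary outcome, ODI, is to be analysed by baseline-adjusted ANCOVA. Repeated outcomes go to a linear mixed model with baseline as a covariate and participant random intercepts. Table 1 schedules ODI at weeks 0, 4, 8 and 16.

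**The concern.** A missing-data plan should fix one analysis of the primary outcome before the data are seen. Here the method depends on which sentence is followed, and no sentence takes precedence. Rules 2 and 3 also change the method at a dropout count known only at the end: 5 of 106 is 4.7% and 6 of 106 is 5.7%, so a single patient moves the trial from LOCF to multiple imputation.

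Two things are at stake. A per-protocol analysis no longer compares the groups as randomised, and it would enter when losses are heaviest and that protection matters most. LOCF assumes that nothing changes after the last visit. No ODI is scheduled between weeks 0 and 4, so a patient lost before week 4 keeps the baseline score. Yet the article gives every patient manual therapy, which its Introduction credits with short-term relief and a high recurrence rate, followed by four weeks of exercise. Change after the last visit is therefore plausible in both arms.

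**Working it through.** **1. Which rule applies at the planned dropout**

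Inputs from the article: N = 106, 53 per arm, 20% dropout, thresholds of 5% and 10%.

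- 5% of 106 = 5.3, so rule 2 moves to multiple imputation at 6 dropouts.
- 10% of 106 = 10.6, so rule 3 applies from 11.
- 20% of 106 = 21.2 expected dropouts.

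Exact binomial probabilities on 106 patients:

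| True dropout | P(below 5%) | P(above 10%) |
|---|---|---|
| 10% | 0.04 | 0.50 |
| 15% | 0.0008 | 0.935 |
| 20% | 0.000007 | 0.997 |

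At the planned rate, rule 1 gives LOCF, rule 2 gives multiple imputation and rule 3 gives per-protocol analysis. LOCF under rule 2 would almost never be used.

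**2. What LOCF does if rule 1 governs**

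The article gives no SD, no expected ODI change within arms, no baseline correlation and no dropout rate by arm. All are assumed below. For scale, 106 × 0.8 / 2 ≈ 42 per arm at 90% power implies SD = 3.57 × √(42/2) / (1.960 + 1.282) ≈ 5.05. SD 10 is shown as well.

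With no treatment effect and dropout unrelated to outcome:

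false difference = (dropout in one arm − dropout in the other) × mean change missed after the last observation

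| Shared improvement | 25% vs 15% | 30% vs 10% |
|---|---|---|
| 0 points | 0 | 0 |
| 5 points | 0.10 × 5 = 0.5 | 0.20 × 5 = 1.0 |
| 10 points | 0.10 × 10 = 1.0 | 0.20 × 10 = 2.0 |
| 20 points | 0.10 × 20 = 2.0 | 0.20 × 20 = 4.0 |

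The arm with more dropout looks worse. The planned effect is 3.57 points, so 1.0 point is 1.0/3.57 = 28% of it.

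Baseline-adjusted ANCOVA was simulated with no effect, 53 per arm, baseline carried forward, a 10-point shared improvement and correlation 0.6:

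| Dropout | False difference | Type I error, SD 5 | Type I error, SD 10 |
|---|---|---|---|
| 25% vs 15% | about 1.0 | 14–16% | 9% |
| 28% vs 12% | about 1.6 | 32–34% | 17–18% |

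The ranges cover repeated runs. With 25% versus 15% dropout and no mean change, the bias is 0 and type I error about 5%.

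**3. Equal dropout is not safe either**

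With 20% dropout in both arms and a true effect of 3.57, LOCF retains about 0.8 × 3.57 = 2.86 points. Simulation (SD 5.05, correlation 0.5, 10-point improvement in controls) gave about 2.8. Power was about 63%, against about 95% for ANCOVA on observed cases.

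**4. LOCF where rule 2 allows it (at most 5 dropouts)**

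Same model as step 2, SD 5 or 10:

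| Split of 5 dropouts | False difference | Type I error |
|---|---|---|
| 3 vs 2 | 0.19 | 3–4% |
| 4 vs 1 | 0.57–0.59 | 6–8% |
| 5 vs 0 | 0.93–0.94 | 16% (SD 5), 8% (SD 10) |

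Only the extreme split comes near the figures in step 2.

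**The case against.** The best defence is that rule 2 is the more specific sentence. It names dropout cases and, at 20% dropout, leads to multiple imputation, which is a sound choice. Rule 1 could then be meant for scattered gaps only. That reading is possible, but the article does not state it. It also leaves rule 3 unresolved.

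It does rule out three stronger readings that a reader might infer.

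- *The analysis rests on LOCF.* This is true of rule 1 only.
- *LOCF gives a false difference whenever dropout differs between arms.* It does not. The mean must also change after the last observation, or the dropouts must follow a different course.
- *The inflated error rates are to be expected in this trial.* They arise only if rule 1 overrides rule 2, and every input behind them is assumed.

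Nor do the documents suggest that analysts could steer the result by group: assessors, data managers and analysts are blinded, and the thresholds depend on dropout, not on outcomes. Finally, the article does not say whether the per-protocol analysis replaces the intention-to-treat analysis or accompanies it. If it only accompanies it, that conflict disappears, but the sentence is written as a switch and needs the clarification.

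**Conclusion.** The point holds as a conflict between stated rules, not as a claim that LOCF will distort this trial. That the three rules diverge at the planned dropout follows from the article's own figures: about 21 expected dropouts against triggers at 6 and 11, with probability 0.997 of passing the second if true dropout is 20%. The LOCF bias is conditional on rule 1 governing and on the assumed change, SD, correlation and dropout split. It ranges from 0 with no mean change to 1.0 point in the 25% versus 15%, 10-point illustration, and more in harsher ones. It should be corrected before analysis, because following the text literally can give a biased or non-randomised primary comparison, and the remedy uses methods the article already names.

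**What to change.** Delete the unconditional LOCF sentence, the 5% threshold and the switch to per-protocol analysis above 10%. Deleting only the LOCF wording would leave the conflict with intention-to-treat in place. Then state one primary rule for all randomised patients, at every dropout rate, under missing at random. Either will do:

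- multiple imputation by arm, using all ODI visits, feeding the planned baseline-adjusted ANCOVA; or
- the baseline-adjusted mixed model already described, named as the primary ODI analysis, with the group contrast at the primary time point.

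The choice must be explicit. As written, the mixed model is not the primary analysis, and ANCOVA at a single visit omits anyone missing that visit unless values are imputed.

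Keep per-protocol analysis, and LOCF if wanted, only as labelled sensitivity analyses. A delta-adjusted sensitivity analysis is optional and may sit in the analysis plan.

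The cost is a few sentences and slightly more analysis work in SPSS. The article reports that analysis had not begun. If that still holds, the change can be made and dated before the data are seen.
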